#### Process evaluation analysis

The pre- and post-intervention focus group data will be analyzed as a whole using a mix of text-based content analysis and thematic analysis [51]. Relevant themes connected to how the process was experienced by the various focus groups (participants and stakeholders in the intervention) will be extracted to identify barriers and facilitators during all stages from identifying the actual needs to designing and implement the urban installations.

## Discussion

The aim of this paper was to present the study protocol for the ‘Move the neighborhood study’, including a description of the case, the co-design based development and implementation of urban installations, and measurements to be used in the evaluation of the study. The study is a quasi-experimental intervention study in a Danish deprived neighbourhood in which a co-design approach will be used to develop highly tailored interventions in the form of urban installations. As there are many factors that can influence the results of this type of intervention, designing this study was complex and required us to make a multitude of decisions that will yield a series of benefits, but also will create some challenges that are further discussed below.

### The interdisciplinary collaboration

Creating changes in public open space that have an effect on active living requires involvement of many different participants [14, 18]. Other studies have shown that the more design and planning experiences are shared and have crossed professional barriers, the more likely the participants are to learn and generate valuable ideas, increase quality and flexibility, improve efficiency, and simulate appropriate use of resources [52]. A particular strength of the study presented in this paper is that it was planned and developed as an equal partnership between researchers from multiple fields, each using their core competences to share ideas and jointly complete all tasks in the study. The health researchers are responsible for the evaluation, and the designers, architects, landscape architects and anthropologists are responsible for the development and implementation of the intervention processes in collaboration with local children and seniors. From literature, the difficult point seems to be balancing the many different interests [52]. In our study we have already experienced that the differences between the scientific fields and traditions among the many different researchers involved in the study was challenging to bring together in a joint aim for the study. To solve this challenge we spent much time describing and explaining individual expectations and understanding each other’s views on research. One of the secondary goals of writing this protocol paper was that it forced us to discuss each step of the study and these open-minded dialogues have been beneficial in creating a common understanding of the study.

### Co-designing in deprived neighbourhoods

During the intervention phase principles of co-design will be used to develop and implement tailored interventions. Designing in a partnership between community members and designers has proven to be an effective approach for addressing social and cultural health inequalities in community-based interventions, particularly in deprived communities [53, 54]. Based on our previous experiences we knew that tailoring an intervention to local needs and wishes, and building on local engagement, were both crucial to the success of the intervention [55]. However, this participatory approach leads to a high degree of diversity in the intervention development process, which makes it difficult to plan the implementation and evaluation of the intervention. To be prepared for the many unknown issues that will arise conducting participatory research we tested co-design tools and collected background information about our research context and target groups in the understanding stage of the intervention phase. This information helped us to understand perceived barriers and potentials in the neighbourhood, which was advantageous for the following co-design workshops. For example, we learned that the children in particular were motivated to be involved in the creation of the installations and that the design workshops have to be very well prepared and clearly facilitated to maintain their attention. The seniors were difficult to involve for longer time periods and they had difficulties seeing themselves being part of the implementation phase. These experiences meant that the co-design process for development and implementation in the two sub-studies became more differentiated and more tailored to the specific target groups than originally intended. Our process evaluation will provide novel insights in the role and importance of the participatory co-design processes, tailoring changes to local needs and wishes.

### Learning from a single-case

The single-case study design is not suitable to provide reliable information that can be generalized to a broader population. However, we deliberately chose a single case to allow for a detailed examination where we can follow all intervention stages closely. In line with this, Flyvbjerg argued that even though knowledge cannot be generalized that does not mean that it cannot enter the collective process of knowledge accumulation in a given field [56]. Also in this field the use of case studies is becoming more common. For example, Sallis and colleagues used case studies to illustrate the potential for effective research translation to facilitate health-oriented land-use and transport practices and policies [7]. If our interventions are successful in achieving more active living in this neighbourhood we fully acknowledge that it will be difficult to implement this particular type of interventions on a larger scale. Nonetheless, the extensive evaluation of the use of specific installations will lead to new knowledge that can be used in urban renewal projects in deprived neighbourhoods in the future.

On a more critical note, Copenhagen Municipality will create many changes in the area in the coming years through an urban renewal process [23], so the current study is not the only project that will change public open space in the neighbourhood, which might make drawing conclusions more difficult. In the selection of our intervention location, we collaborated closely with the Areal Renewal Office so that these sites will not be the primary location for other changes to the urban environment in the neighbourhood. Furthermore, the timing and the selected effect evaluation methods, SOPARC observations and GPS in combination with accelerometer, make it possible to investigate changes in use of specific spots independent from the urban renewal projects.

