### Study design

The study is a quasi-experimental community-based intervention study including two sub-studies: 1) a children study and 2) a senior study. Each of the two sub-studies is divided into three phases: 1) pre-intervention; 2) intervention; 3) post-intervention. The intervention phase includes different interlinked co-design steps: understanding, developing and implementing. Information collected during the first co-design step, understanding, will be used to start the second co-design step, developing. In this step researchers and participants will in an iterative process jointly explore and develop ideas where e.g. participant ideas will be visualised by designers and then presented back to participants to improve and decide upon. The ideas will be interpreted and implemented in the final step. The evaluation of the study is separated into an effect evaluation and a process evaluation. The effect evaluation will be conducted pre-intervention (baseline) and post-intervention (follow-up) to assess the effect of the interventions whereas the process evaluation will be conducted before, during and after the intervention phase to describe how the interventions were developed and implemented. To be able to support a comprehensive evaluation of the study, a range of qualitative and quantitative methods will be employed. The study design with its two sub-studies and phases is illustrated in Fig. 1.

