### The neighbourhood

The intervention study takes place in the neighborhood of Sydhavn [the South Harbour] in Copenhagen, Denmark. The neighbourhood has 10,276 inhabitants [23], spans an area of 1.2 km^2^ and is framed by high-traffic corridors [24].

The district was planned and built between 1908 and 1950 in line with the welfare planning ideologies of that time in an effort to provide healthier and better living conditions for the growing work force moving into Copenhagen. With reference to the English garden cities the neighbourhood consists of homogenous 2–3 story brick buildings arranged in geometrical structures punctuated by green boulevards, small parks and public squares [23, 25]. Because of a decline in the number of inhabitants throughout the years the neighbourhood has become a place where socially challenged people are housed by public authorities [23]. Demographically the area is one of Copenhagen most disadvantaged neighborhoods. In this neighbourhood 22.1% of the population stands outside the labour market (17.1% on average in Copenhagen), 32.0% has no formal education (21.3% on average), and 40.2% has a low income (30.6% on average) [23]. With 73.0 years as average life expectancy, the neighbourhood has one of the lowest average life expectancies in Denmark where the average is 80.6 years [26].

As one of the last remaining deprived districts in Copenhagen that has not been subject to urban renewal, the area is selected to undergo large changes in the coming years through a municipal renewal initiative. Copenhagen Municipality will focus their investments in the neighbourhood on renewing urban green spaces, opening a Metro (subway) line in 2022, and a large park renewal project focusing on storm water management [23]. The public open space interventions planned in this study tie into this process, which allows for a close linkage between our intervention study and the municipal urban renewal strategies.

A map of the neighbourhood showing the different intervention sites is presented in Fig. 2.

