#### Effect evaluation

The aim of the effect evaluation is to examine the use of the urban installations developed and implemented with and for children and seniors. The System for Observing Play and Recreation in Communities (SOPARC) was used to systematically observe the use of selected locations in the pre-intervention phase (September–October 2016 and April–May 2017) and observations will take place in the post-intervention phase to systematically observe the use of the new urban installations and surrounding locations (September–October 2017 and April–May 2018). SOPARC is a validated tool to assess the use of public spaces in community settings [43]. SOPARC is used to record gender, age, PA level, primary activity and social interactions for each observed person. The compiled SOPARC data makes it possible to determine the number of users at different times and days of the week, as well as assess user characteristics, activity levels and common activities carried out by users at the observation locations. Furthermore, at the beginning of each observation, weather conditions were recorded and a picture was taken to visualise each area and its features. Observations take place at each of the four intervention sites (see Fig. 2) during three weekdays and one weekend day, four times a day (morning: 7.30–8.30, lunch: 11.30–12.30, afternoon: 15.30–16.30, and evening: 19.30–20.30). SOPARC data was collected over a five-week period by four trained observers and resulted in a total of 64 h of observations. SOPARC baseline data will be used to qualify the co-design workshops in the intervention process of the two sub-studies.

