### Data analysis

#### Effect evaluation analysis

SOPARC data will provide information on how specific places are been used and by whom, before and after the interventions, as well as the specific use of the implemented urban installations. For each observed area the total number of users will be compared, as will the share of children and seniors, the average activity level, and common activities.

The collected GPS and accelerometer data will be merged and processed using the Personal Activity and Location Measurement System (PALMS, https://ucsd-palms-project.wikispaces.com) to match the two types of data based on their timestamp, remove GPS error, classify accelerometer data into activity levels, and detect walking, cycling and vehicle trips. The combined accelerometer and GPS data will be further processed in a PostgreSQL database were GIS (geographic information system) data on all intervention sites, green spaces, and daily destinations will be incorporated as well. This will make it possible to assess which areas and destinations participants visited, how often they did this and how long they stayed. It will furthermore be possible to assess how active participants were during their visit to a location, and which mode of transportation they used to get there (see *Klinker* et al. 2014 for more information on this method) [50]. The differences between baseline and follow-up data will be analysed as repeated cross-sectional measures comparing the number of users, the share of children, the share of seniors, as well as average activity levels.

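### The design cannot support the stated independence from municipal renewal: it compares baseline with follow-up in one neighbourhood, with no comparator in the stated analysis

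*Protocol article*

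**What the plan says.** Under The neighbourhood, the article reports that "the area is selected to undergo large changes in the coming years through a municipal renewal initiative". The municipal work includes green-space renewal, a large park project and a metro line due in 2022. The same section says the study's own installations are tied to this process and closely linked to the municipal strategy.

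Under Study design, "The effect evaluation will be conducted pre-intervention (baseline) and post-intervention (follow-up) to assess the effect of the interventions". Under Effect evaluation, "Observations take place at each of the four intervention sites (see Fig. 2) during three weekdays and one weekend day, four times a day". The SOPARC windows are September–October 2016 and April–May 2017 before the intervention, and September–October 2017 and April–May 2018 after it. Weather is recorded at the start of each observation.

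Under Effect evaluation analysis, GIS "data on all intervention sites, green spaces, and daily destinations will be incorporated as well" with the GPS and accelerometer records. Baseline and follow-up are then compared as repeated cross-sections.

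Under Learning from a single-case, the authors explain that "we deliberately chose a single case to allow for a detailed examination where we can follow all intervention stages closely". They concede that the municipal changes may make conclusions harder to draw, and note that sites were picked with the local renewal office so as not to be the main location of other works. They then state that timing and the chosen methods "make it possible to investigate changes in use of specific spots independent from the urban renewal projects".

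**The concern.** The last statement tells the reader that the confounding just conceded has been dealt with. What it relies on is mainly precision about place: SOPARC and GPS show where use changed, by how much and among whom. They do not show why. A change at an intervention site between 2016/17 and 2017/18 could come from the installation, from renewal of spaces nearby, from people displaced by that renewal, or from an ordinary difference between years. Measuring the spot more finely leaves all of these in the estimate.

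The baseline-to-follow-up comparison is the only contrast described for assessing the effect of the interventions. If the independence sentence stands, a background rise in outdoor use would be credited to the installations and a background fall would hide a real gain, and readers would have been told that neither can happen.

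**Working it through.** **1. Where baseline SOPARC was done.** The article speaks first of selected locations and then describes observation at the four intervention sites. The reported total settles the matter. Inputs (Effect evaluation): 4 sites; 3 weekdays + 1 weekend day = 4 days; 4 slots of 1 hour each.

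4 × 4 × 4 × 1 h = 64 h, which equals the stated total.

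On the same schedule one comparison site would have made it 5 × 16 = 80 h, and four would have made it 8 × 16 = 128 h. The intervention sites use up all 64 hours, so no baseline observation exists elsewhere.

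**2. What a baseline-to-follow-up ratio estimates.** Without a comparator,

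observed ratio = installation effect × background change.

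This is one equation with two unknowns. An observed ratio of 1.20 fits each of these equally well:

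| Background change (assumed) | Implied installation effect |
|---|---|
| 0.90 | 1.20 / 0.90 = 1.33 |
| 1.00 | 1.20 / 1.00 = 1.20 |
| 1.10 | 1.20 / 1.10 = 1.09 |
| 1.20 | 1.20 / 1.20 = 1.00 |

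Nothing in the stated analysis chooses between the rows.

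**3. How often a background change alone would look significant.** The article gives no user counts, no trend and no test, so every input here is an assumption: 5 to 20 users per hour, 64 h in each phase, overdispersion φ from 1 to 6, no installation effect, and a two-sided 5% Wald test on the log rate ratio with SE = √(φ/μ₀ + φ/μ₁).

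Worked case: 5 users per hour, φ = 1, background +10%. Then μ₀ = 64 × 5 = 320, μ₁ = 352, SE = √(1/320 + 1/352) = 0.077 and ln 1.10 = 0.095, so z = 1.23 and the probability of rejection is 0.235.

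| Background change | Apparent ratio | Probability of a significant result over the range |
|---|---|---|
| 0% | 1.00 | 5% |
| +10% | 1.10 | 8% to 69% |
| +20% | 1.20 | 17% to over 99% |

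The low end is 5 users per hour with φ = 6; the high end is 20 users per hour with φ = 1. The table shows direction and sensitivity. It does not forecast this study.

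**4. What the stated safeguards cover.**
- *Site choice* lowers the chance of direct works at the sites. Not being the main location is weaker than being untouched, and it does not prevent spillover or displacement from renewed spaces nearby.
- *Season-matched windows* deal with season, but not with differences between years.
- *Weather recording* would allow some adjustment for weather, but not for renewal.
- *Timing* excludes the metro opening (2022, after the last window in April–May 2018). The green-space and park works carry no date that excludes overlap.

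**5. Whether nearby green spaces could be subtracted.** Suppose participants move 10 minutes from another green space to an intervention site and do nothing new. The site changes by +10 and the other space by −10, so the difference-in-differences is +10 − (−10) = +20 although total activity changes by 0. Subtraction counts relocation twice. Showing the three quantities side by side does not.

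**The case against.** The strongest reply is that the sentence is modest. It speaks of investigating changes in use at particular spots, it follows an open caveat, and the stated aim of the effect evaluation is to examine use of the installations. Someone observed using a structure that did not exist at baseline is using that structure, whatever else changed in the neighbourhood. This stands for direct use of the installations. It does not cover total users, age shares or activity levels at a site, which are also to be compared, and Study design gives the purpose as assessing the effect of the interventions.

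The safeguards in step 4 are real and should be credited. They support saying that the influence of the renewal is reduced; they do not support saying that the findings are independent of it.

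A reader might go further in three ways that the documents do not support:
- *That the whole effect evaluation is confined to the intervention sites.* That is true only of baseline SOPARC. Follow-up SOPARC also covers the surroundings, and GPS follows participants into other green spaces and daily destinations. Under Measurements, GPS with accelerometer is meant to tell relocated from new activity, which is a useful but different question from what caused a change.
- *That the bias has a known size.* No background trend is given.
- *That a within-participant difference-in-differences should become the main analysis.* The article plans repeated cross-sections and does not promise that the same device wearers return; it also reports that seniors were hard to retain. Subtracting nearby spaces has the fault shown in step 5. Nor can seniors at the children's sites, or children at the seniors' sites, serve as untreated SOPARC groups, since both would meet new installations.

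**Conclusion.** The point holds against the independence statement. The stated effect contrast is an uncontrolled baseline-to-follow-up comparison in one neighbourhood, baseline SOPARC has no site outside the intervention, and no stated analysis uses the wider GPS/GIS data as a comparator. The stated safeguards reduce confounding by concurrent renewal and by year-to-year change without removing it.

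The bias in a site-level ratio equals the background change that reaches the site. The documents cannot say how large that is; the 10% and 20% figures are assumptions. The conclusion does not depend on them, only on the absence of a comparator. An unshown analysis plan might use other green spaces as a reference, but the sentence rests its claim on timing and measurement methods, and these cannot carry it.

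This does not make the evaluation worthless. Observed use of the installations can still be reported as specific to them.

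**What to change.** 1. **Replace the sentence under Learning from a single-case.** Suggested wording: *Site choice and timing reduce the influence of concurrent urban renewal, but pre-post changes in site use cannot be fully separated from it.* Limit the conclusions to match. Use of the installations themselves may still be reported as specific to them.

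2. **Add a descriptive comparison series from the GPS/GIS data already planned.** Report the baseline-to-follow-up change in time and activity (a) at the intervention sites, (b) at green spaces that are neither intervention sites nor being renewed, and (c) in total. Present the three side by side as repeated cross-sections, with within-participant changes only for people measured twice. If (a) rises while (b) falls and (c) is flat, that points to relocation; if (a) and (b) rise together, it points to a background change. Do not make (a) minus (b) the primary estimate.

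3. **Do not use the other age group at each site as a SOPARC control.**

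The cost is one rewritten sentence, a record of which green spaces were renewed and when, and some further database queries. No data collection is needed beyond what is planned. The price is a less favourable causal statement.

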### Measurements

Combining an effect evaluation and a process evaluation and collecting different types of data that complement each other is a strength of this study [17].

A novel aspect of our study is the combination of using SOPARC, accelerometer and GPS to determine our two target groups’ use of the new urban installations. Previously, a number of studies have used systematic observations to evaluate public open space interventions [57]. To our knowledge, using systematic SOPARC observations, accelerometer and GPS in combination has not been used before in longitudinal studies evaluating public open space interventions in neighbourhoods. Using accelerometer and GPS in combination has the potential to assess whether a change in active living is “relocated” activity (i.e. the same activity, but in a different location), or if it is a true increase in active living [55]. These methods also have the advantage that each individual is identifiable, which means that it is possible to adjust the analyses for different personal characteristics [50]. However, when using accelerometer and GPS no information about use of the newly built installations is obtained if our participants do not use the installations. Furthermore, the combination of accelerometer and GPS is relatively invasive for participants, which can complicate recruiting participants in the study and get sufficient valid data. Recruitment of children happened trough the local school and was relatively easy once the co-design collaboration had been put into place. However recruitment of seniors to wear the devices was highly challenging, despite our large efforts. Therefore, we supplemented our accelerometer and GPS data by collecting SOPARC data, which is much less invasive. SOPARC observations provide an overall picture of the use of specific areas and in the follow-up observations this method can provide information about the use of the specific urban installations that were built. Even though SOPARC is an objective observation tool, there might occur differences between different observers conducting the SOPARC observations. Especially age can be difficult to access by looking at a person for a few seconds. We have tried to compensate for that by having a workshop where the observers were trained in how to observe and assess age. After the training, all observers had to observe the same area at the same time and results were found to be comparable.

The information from the focus groups and the observation of workshops will be used to describe how the intervention has been implemented [49]. To get the most comparable baseline and follow-up viewpoints from the participants our intension is to include the same participants in our focus groups before and after intervention. However, in the understanding phase we found that it is very difficult to recruit and sustain seniors for longer time-periods, which may influence our recruitment of seniors for the follow-up focus group. For that reason, it is important to continue involving local stakeholders in study-related activities and meetings throughout the study to maintain the established links between researchers and community members [29].

